#### 8.1.2.4 Cranial Ultrasound

Cranial ultrasound studies (cUS) will assess neurological complications for the medium-term efficacy assessment. Severe neurological complications are defined based on worst cranial ultrasound (cUS) scan appearances detected on any one of a series of cUS scans that are routinely performed in these infants up to 36±2 weeks PMA. Severity of cUS imaging is to be graded using a modified score published by the SafeBoosC trial (1-4). Severe brain injuries will be cerebral haemorrhage grade II or III, periventricular haemorrhagic infarction, white matter injury, post-haemorrhagic ventricular dilatation, cerebellar haemorrhage, or cerebral atrophy.

It is strongly recommended to perform a first cUS scan as soon as possible at screening, preferably within the first 6 hours from birth and before treatment is started. Subsequent scans will be done when clinically indicated.

Only two cUS proformas should be filled in: baseline cUS performed during the screening phase (if available); and worst cUS findings detected on any of cUS scans up to 36±2 weeks PMA.

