D: Included bronchopulmonary dysplasia, necrotizing enterocolitis, retinopathy of prematurity and cUS diagnosis of severity of brain damage (cerebral haemorrhage grade II or III, periventricular haemorrhagic infarction, white matter injury, post-haemorrhagic ventricular dilatation, cerebellar haemorrhage, or cerebral atrophy).

- a) Infants are screened for inclusion into the study within 0-72 hrs of birth. Screening Visit finishes when infant is enrolled and allocated (Baseline Visit). Sign informed consent form prior to any assessment in the trial and record date of signing the informed consent form; except in the case of deferred consent.
- b) Infants that fulfil inclusion criteria are allocated to intervention; provided there are no exclusion criteria according to protocol.

X\*\*: Growth assessment (weight, height and head circumference), general health, structured neurological examination and neurodevelopmental testing included.

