##### *8.1.1.2 Enrolment: Baseline Visit*

If the inclusion criteria are met, and there are no reasons for exclusion, the infant is then enrolled into the trial and allocated to a dosage regimen according by the study statistician. At this point the Screening Visit finishes and the Baseline Visit parameters outlined in section 8.1.2.3 below are assessed.

The study intervention should be initiated straight away after the Baseline Visit always within the first 72 hours from birth.

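### Severe neurological complication is the worst cranial ultrasound on any scan, with no start to the window, so a lesion already present before dobutamine counts as a case of a secondary outcome

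*Protocol*

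**What the plan says.** Section 8.1.2.4 of the protocol gives the purpose of the scans: "Cranial ultrasound studies (cUS) will assess neurological complications for the medium-term efficacy assessment". It then defines the outcome: "Severe neurological complications are defined based on worst cranial ultrasound (cUS) scan appearances detected on any one of a series of cUS scans". The form that captures it records "worst cUS findings detected on any of cUS scans up to 36±2 weeks PMA". The listed lesions include haemorrhage of grade II or III, and the list is not limited to new or progressed lesions.

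The same section encourages a scan before treatment but does not require one: "It is strongly recommended to perform a first cUS scan as soon as possible at screening", preferably within 6 hours of birth. Only two forms are to be completed, and the first is the "baseline cUS performed during the screening phase (if available").

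In section 1.2 (Schedule of Assessments), item D, marked in the secondary outcomes row at the mid-term visit, includes the "cUS diagnosis of severity of brain damage". On timing of treatment, section 8.1.1.2 says: "The study intervention should be initiated straight away after the Baseline Visit always within the first 72 hours from birth".

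**The concern.** An outcome that is meant to inform on treatment should be able to occur only after treatment has begun. Here the window has an upper limit and no lower one. The screening scan, where it exists, is one of the scans over which the worst finding is taken. A grade II haemorrhage seen at screening and unchanged thereafter makes the infant a case.

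There is no untreated or placebo group in which the same pre-existing injury would appear and against which it could be set off. The reported proportion would mix injury present at entry with injury arising later, and a reader could not tell how much of each it contained. The planned group sizes are small, so one or two such infants would visibly move a proportion tabulated by dose.

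**Working it through.** The protocol states no figure for this outcome, so there is nothing to reproduce. The point rests on reading the sections together; the arithmetic only illustrates its size.

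**Step 1. Does anything remove a lesion present at entry?**

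- Outcome definition and worst-finding form (section 8.1.2.4): end at 36±2 weeks PMA, no start, no condition that the lesion be new.
- Baseline form (section 8.1.2.4): collected only where a screening scan was done; no rule subtracts it from, or compares it with, the worst finding.
- Exclusion criteria (section 5.2): none concerns cranial ultrasound or haemorrhage, so an infant with a lesion at entry can be enrolled.
- Start of infusion (section 8.1.1.2): as late as 72 hours from birth, so there is time for a lesion to precede it.

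Nothing removes it. Followed as written, the definition counts it.

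**Step 2. How does the protocol treat the same lesion elsewhere?** Section 8.3.1 extends adverse events to events that first appear, and earlier conditions that become more severe or more frequent, after study drug. Section 8.3.4 starts collection at allocation. An unchanged haemorrhage present at entry is therefore no adverse event, yet it is a severe neurological complication under section 8.1.2.4.

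**Step 3. Can the two forms separate the lesions afterwards?** Partly. Where a screening scan exists, its finding is on the baseline form. A lesion first seen on a later scan that still precedes the infusion would, unless that scan fills the baseline form, appear only as the worst finding. Section 8.1.2.4 does not say which screening scan fills the baseline form, nor that the time of the worst scan is recorded.

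**Step 4. Illustration of size.** From section 9.1.1: maximum 30 infants, planned as 5 + 9 + 12 + 4 + 0 = 30 over the five doses. Assumed, because the documents give neither: prevalence at entry b = 5%, 10% or 20%, and risk of a new lesion in infants clear at entry t = 10%.

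- Expected pre-existing cases = 30 × b
- Probability of at least one among n infants = 1 − (1 − b)^n
- Proportion counted under the any-scan rule = b + (1 − b) × t
- Share of counted cases present at entry = b / [b + (1 − b) × t]

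| b | 30 × b | At least one of 30 | At least one of 12 | Counted, any scan | Share present at entry |
|---|---|---|---|---|---|
| 5% | 1.5 | 78.5% | 46.0% | 14.5% | 34.5% |
| 10% | 3.0 | 95.8% | 71.8% | 19.0% | 52.6% |
| 20% | 6.0 | 99.9% | 93.1% | 28.0% | 71.4% |

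For b = 10%: 0.10 + 0.90 × 0.10 = 0.19, and 0.10 / 0.19 = 52.6%. Counting only new lesions among infants clear at entry would give 10% in every row.

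One pre-existing case adds 1/5 = 20 percentage points in the planned group of 5, and 1/12 = 8.3 points in the group of 12.

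**The case against.** The strongest reply is that little depends on this outcome. Cranial ultrasound is not among the objectives and endpoints of section 3, and no analysis in section 9 uses it. Section 8.1.1.8 describes the mid-term visit as a recording of neonatal outcomes. A worst-ever finding kept beside a baseline record is a defensible description, and choosing between worst-ever, new and progressed lesions is often left to a statistical analysis plan. The comparison of harm between doses that is planned, on adverse events (section 9.1.2), already follows the new-or-worse rule.

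Much of this stands, and it limits the point. Three stronger readings are tempting and are not supported:

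- A reader might infer that the trial's main result is affected. It is not: the primary endpoint is SVC flow, and neither dose allocation nor sample size uses cranial ultrasound.
- A reader might infer that chance imbalance in lesions at entry would pass for a dose effect in a planned test. No between-dose ultrasound test is planned. The risk lies in how a table by dose is read.
- A reader might infer that 72 − 6 = 66 hours without drug routinely follow the baseline scan. That is an extreme. Six hours is a preference, and the baseline form takes a scan from the screening phase, which lasts until enrolment.

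Two parts of the reply do not stand. The definition is not left open for a later document: section 8.1.2.4 states it and assigns it to efficacy, and the schedule marks it as a secondary outcome. The adverse event analysis is also no full substitute, since collection stops 30 days after the drug is stopped (section 8.3.4), which need not reach 36±2 weeks PMA.

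**Conclusion.** The point holds within limits. The definition counts listed lesions that were present before dobutamine, in an uncontrolled outcome labelled as efficacy, and it departs from the protocol's own adverse event rule. That conclusion follows from the wording and needs no assumption. The size does: with assumed prevalences at entry of 5% to 20%, 1.5 to 6 of 30 infants would be such cases, and the documents cannot narrow that range. The by-dose percentages also use planned group sizes, which may change as doses are reassigned. The consequence is confined to the interpretation of this secondary outcome, so this is a cheap improvement and not a flaw in the dose-finding result.

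**What to change.** In section 8.1.2.4, define the outcome as a listed lesion that is new or has progressed relative to the pre-treatment scan. For graded haemorrhage, progression is a higher grade; for lesions listed without grades, the criterion is that the lesion is newly present. A requirement of at least one grade of worsening for every item would not fit the ungraded ones.

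Complete the baseline form from the last available scan before the effective start of infusion (t0), and record the date and time of the scan on both forms. Report *present before t0* and *no scan before t0* as separate categories, and keep the worst-ever finding as a descriptive line. Moving the start of the window to t0 would not be enough alone, because a haemorrhage present at entry can still be visible on later scans.

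The cost is a change of wording and a small eCRF addition: scan date and time, and a rule on which scan fills the baseline form. The existing two forms do not suffice without these. The downside is a third category for infants without a pre-treatment scan, whose lesions cannot be dated. No extra scan is needed.

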#### 8.1.2.5 Pharmacogenetic

To analyse the pharmacogenetics of GNAS1 and β1-adrenoceptor polymorphism and different metabolizer enzymes of dobutamine we will be gained buccal swabs.

The scraping samples of the oral mucosa will be obtained at enrolled in the study by the nursery staff. A cotton swab will be applied gently to both cheeks up and down with a double-tipped, sterile swab. The buccal swab will be removed and placed back in the sterile tube.

#### 8.1.2.6 Standard of Care Study Procedures

There will be no per-protocol concomitant medication or treatment. Accordingly, other important co-interventions will follow specific centre protocols and will be recorded in the case record form (eCRF).

All trial related procedures will be undertaken in line with local procedures to minimise pain and optimise welfare. All trial-related procedures will be conducted by professionals experienced in neonatal care who have received trial-specific training. Non-pharmacological (behavioural) and pharmacological analgesic measures (sucrose, paracetamol, and opiates) will be preferably used in accordance with local guidelines and the condition of the baby at the time of the procedure. Blood sample volumes will be minimised.

## 8.2 SAFETY AND OTHER ASSESSMENTS

The safety of the study intervention will be evaluated, as a secondary endpoint, by recording and comparing the absolute and relative frequencies of Adverse Events (AEs) and Serious Adverse Events (SAEs) for the whole study population and for the five treatment groups.

Pharmacovigilance definitions and processes for this purpose are defined in section 8.3, while the intended statistical analysis of safety as a secondary endpoint is described in section 9.1.2.

## 8.3 ADVERSE EVENTS AND SERIOUS ADVERSE EVENTS

### 8.3.1 Definition of Adverse Events (AE)

#### **Adverse Event (AE):**

Any untoward medical occurrence in a patient or clinical investigation patients administered a medicinal product, which does not necessarily have a causal relationship with this treatment (the study medication).

An AE can therefore be any unfavourable and unintended sign (including an abnormal laboratory finding), symptom or disease temporally associated with the use of the study medication/procedure, whether considered related to the study medication.

This includes any newly occurring event, or a previous condition that has increased in severity or frequency since the administration of study drug.

#### **Adverse Reaction (AR):**

All untoward and unintended responses to a medicinal product related to any dose administered.

Unlike Adverse Events, a causal relationship between a study medication and an AE is considered at least a reasonable possibility, i.e., the relationship cannot be ruled out.

### 8.3.2 Definition of Serious Adverse Events (SAE)

#### **Serious Adverse Event (SAE) or Serious Adverse Reaction (SAR):**

A serious adverse event is any untoward medical occurrence that at any dose:

- Results in death,
- Is life-threatening. (NOTE: The term "life-threatening" in the definition of "serious" refers to an event in which the participant was at risk of death at the time of the event; it does not refer to an event which hypothetically might have caused death if it were more severe).
- Requires inpatient hospitalization or prolongation of existing hospitalization,
- Results in persistent or significant disability/incapacity, or
- Is a congenital anomaly/birth defect.
- Other important medical events. NOTE: Other events that may not result in death are not life threatening, or do not require hospitalization, may be considered a serious adverse event when, based upon appropriate medical judgment, the event may jeopardize the patient and may require medical or surgical intervention to prevent one of the outcomes listed above.

To ensure no confusion or misunderstanding of the difference between the terms "serious" and "severe", which are not synonymous, the following note of clarification is provided:

The term "severe" is often used to describe the intensity (severity) of a specific event (as in mild, moderate, or severe myocardial infarction); the event itself, however, may be of relatively minor medical significance (such as severe headache). This is not the same as "serious," which is based on patient/event outcome or action criteria usually associated with events that pose a threat to a participant's life or functioning as defined in the bullet points above. Seriousness (not severity) serves as a guide for defining regulatory reporting obligations.

### 8.3.3 Classification of an Adverse Event

#### 8.3.3.1 Severity of Event

The following guidelines will be used to describe severity of the adverse events (AEs):

- **Mild** – Events require minimal or no treatment.
- **Moderate** – Events result in a low level of inconvenience or concern with the therapeutic measures. Moderate events may cause some interference with functioning. Some assistance may be needed, no or minimal medical intervention.
- **Severe** – May require systemic drug therapy or other treatment. Severe events are usually potentially life-threatening or incapacitating. Of note, the term “severe” does not necessarily equate to “serious”.

#### 8.3.3.2 Relationship to Study INTERVENTION

All adverse events (AEs) must have their relationship to study intervention assessed by the clinician who examines and evaluates the participant based on temporal relationship and his/her clinical judgment. The degree of certainty about causality will be graded using the categories below. In a clinical trial, the study product must always be suspect.

- **Related** – The AE is known to occur with the study intervention, there is a reasonable possibility that the study intervention caused the AE, or there is a temporal relationship between the study intervention and event. Reasonable possibility means that there is evidence to suggest a causal relationship between the study intervention and the AE.
- **Not Related** – There is not a reasonable possibility that the administration of the study intervention caused the event, there is no temporal relationship between the study intervention and event onset, or an alternate etiology has been established.

#### 8.3.3.3 Expectedness

Investigators at sites will be responsible for determining whether an adverse event (AE) is expected or unexpected. An AE will be considered unexpected if the nature, severity, or frequency of the event is not consistent with the risk information previously described for the study intervention.

##### **Unexpected adverse reaction:**

An adverse reaction, the nature or severity of which is not consistent with the applicable product information.

##### **Suspected Unexpected Serious Adverse Reaction (SUSAR):**

Serious adverse drug reaction (SAR) that is unexpected or for which the development is uncommon (unexpected issue) observed during a clinical trial and for which there is a relationship with the study drug.

These adverse drug reactions, characterized to be serious and unexpected, are mandatory to be communicated immediately in accordance with national legislation and international guidelines.

### 8.3.4 Time Period and Frequency for Event Assessment and Follow-Up

The investigator will monitor and systematically collect all the AEs from the time of **allocation** until **30 days after the patient has been stopped the administration of the drug**.

All AEs spontaneously reported by the patient parents and/or in response to an open question from study personnel or revealed by observation, physical examination, or other diagnostic procedures will be recorded in the history. Adverse events that were related with the study medications (AR and SAR) or not related but serious (SAE) will be collected on the appropriate page of the eCRF.

All adverse events will be monitored until they are resolved or stabilized. All adverse events that persist once the study is over will also be monitored until their final evolution is determined.

It will be left to the investigator's clinical judgment whether an AE is of sufficient severity to require the participant's removal from treatment. An infant's parents/legal representative may also voluntarily withdraw from treatment due to what he or she perceives as an intolerable AE. Whether either of these occurs, the participant must undergo an end of study assessment and be given appropriate care under medical supervision until symptoms cease or the condition becomes stable.

---

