| Assess eligibility criteria                     |                                                      | X                      |                    |                                                  |                                     |                           |                             |                |                     |                                             |
| Record demographic, maternal and perinatal data |                                                      | X                      |                    |                                                  |                                     |                           |                             |                |                     |                                             |
| Dose regimen assignment                         |                                                      |                        | X                  |                                                  |                                     |                           |                             |                |                     |                                             |
| Assessment of Adverse Events                    |                                                      |                        |                    | X                                                | X                                   | X                         | X                           | X              |                     |                                             |
| Circulatory failure evaluation                  | BP (Mean, Syst. Diast.)                              | X*                     | X                  | X                                                | X                                   | X                         | X                           | X              |                     |                                             |
|                                                 | Lactate                                              | X*                     | X*                 | X*                                               | X*                                  | X*                        | X*                          | X*             |                     |                                             |

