| Secondary                                                                                                                                                                                                                                                                                                                                       |                                                                                                                                                                                                                                                                                                                                                                                         |
| 
 
• To assess the proportion of infants who maintain an acceptable haemodynamic status with the dobutamine infusion alone in the first 72h from birth (efficacy).
 
• To evaluate the safety of dobutamine for the whole study population as well as for the seven treatment groups separately.
 
 | 
 
• Proportion of neonates achieving and maintaining a clinically acceptable haemodynamic status [B] with the dobutamine infusion alone in the first 72 hours from birth.
 
• Absolute and relative frequencies of adverse events (AEs) and severe adverse events (SAEs), to be recorded and compared between groups.
 
 |

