#### 8.3.5 Adverse Event Reporting

All **Adverse Events (AEs)** that occur during the trial will be documented in the patient's medical history. AEs that were related with the study medications (AR and SAR) or not related but serious (SAE) will be collected on the appropriate page of the eCRF, the following information about the AEs will be recorded: description, start and end date, severity, seriousness, evaluation in relation to the investigation drug, actions taken and outcome.

Any pre-existent illness exacerbation that occurs after drug study initiation should be considered as an adverse event.

Any abnormal lab result that the investigator considers clinically important and that requires study drug dose adjustment, transitory or permanent study drug discontinuation or any other interventional measure or diagnostic evaluation for patient risk evaluation will be collected as an adverse event and should be investigated and monitored appropriately.

**Serious Adverse Reaction (SAR)** that occur during the trial must be **notified to the sponsor** within a maximum period of 24 hours from the time of knowing about the event.

Also, the investigator shall complete and sign the SAR report form and send it by fax or email to:

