#### Safety:

Safety analysis will be conducted for the whole study population as well as for the five treatment groups separately. AEs and SAEs will be reported with absolute and relative frequencies per treatment group along with the corresponding 95% CIs (two-sided). Differences between different groups (each of the dose regimens separately) will be compared using Chi-squared Test. For all comparisons 95% CIs (two-sided) will be provided.

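### The safety endpoint counts all adverse events, but the stated eCRF rule leaves out non-serious events judged unrelated

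*Protocol*

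**What the plan says.** **What is to be estimated.** Section 3, like the synopsis in 1.1, gives the safety endpoint as "Absolute and relative frequencies of adverse events (AEs) and severe adverse events (SAEs), to be recorded and compared between groups". Section 8.2 describes the safety evaluation as "recording and comparing the absolute and relative frequencies of Adverse Events (AEs) and Serious Adverse Events (SAEs) for the whole study population"; it names the five dose groups as well. The Safety paragraph of 9.1.2 plans frequencies per group with two-sided 95% intervals and a chi-squared comparison of the dose groups. None of these places restricts the AEs to related ones, and the AE definition in 8.3.1 does not require a causal link to the drug.

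**What is to be collected.** Section 8.3.4 opens broadly: "The investigator will monitor and systematically collect all the AEs from the time of" allocation, up to 30 days after the drug is stopped. Section 8.3.5 then places all AEs in the notes (they are events "that occur during the trial will be documented in the patient's medical history"). Both sections limit the eCRF to those "related with the study medications (AR and SAR) or not related but serious (SAE) will be collected on the appropriate page of the eCRF".

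**What points the other way.** Section 6.2 sends conditions that arise or worsen and are treated to the AE page of the eCRF, with a when-applicable qualifier and a reference back to the safety section. The Schedule row "Assessment of Adverse Events" carries a plain X from start of infusion through the end-of-treatment and 72-hour visits. The legend defines X as a mandatory procedure to be entered in the eCRF.

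**The concern.** The endpoint and the capture rule describe different sets of events. If the eCRF is the analysis source, the figure reported as AE frequency would in fact be adverse reactions plus SAEs.

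This matters beyond labelling because the filter is a judgement. Section 8.3.3.2 gives the causality decision to the examining clinician, and section 6.1.1 says that dose cannot be concealed from carers or assessors. For a non-serious AE, entry into the data can therefore depend on an opinion formed with the dose known, and the resulting rates are then compared between doses. Such a filter could create a dose difference or hide one.

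A separate analysis plan could not repair this, since it cannot analyse events that were never entered. The protocol nowhere says that the safety analysis will draw on the medical notes.

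**Working it through.** The plan states no figure on this point, so there is none to reproduce. The check is a reconciliation of text, followed by a labelled illustration.

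**Step 1. Which AEs pass the 8.3.4/8.3.5 rule?**

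| | Judged related | Judged unrelated |
|---|---|---|
| Serious | eCRF (SAR) | eCRF (SAE) |
| Non-serious | eCRF (AR) | notes only |

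Three of the four cells reach the eCRF. Both serious cells do, so SAE counts do not depend on the causality judgement. The all-AE count does.

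**Step 2. Do other parts of the protocol fill the empty cell?** In part. Section 6.2 would bring in treated conditions whatever their causality, but it qualifies this and defers to the safety section, where the restriction sits. The Schedule legend implies eCRF entry of the AE assessment without saying which AEs. Neither overrides a restriction stated twice, so the texts conflict.

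**Step 3. How large could the loss be?** Let s be the share of AEs that are serious and r the probability that a non-serious AE is judged related. Under the restricted rule,

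captured share = s + (1 − s) × r.

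The documents give neither s nor r; every value below is an assumption.

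- With s = 0.2: r = 0.3 gives 0.2 + 0.8 × 0.3 = 44%; r = 0.5 gives 60%; r = 0.7 gives 76%; r = 0.9 gives 92%; r = 1 gives 100%.
- Over s from 0.1 to 0.5 and r from 0.1 to 1, the share runs from 0.1 + 0.9 × 0.1 = 19% up to 100%.

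A range that wide, with no loss at its upper end, means the documents do not support an estimate.

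**Step 4. Can the filter distort a dose comparison?** Assume a true AE risk of 60% at every dose, one AE per infant, and s = 0.2. If r is 0.5 at both a low and a high dose, the recorded rate is 0.6 × 0.60 = 36% at each. If r is 0.3 at the low dose and 0.7 at the high dose, the recorded rates are 0.6 × 0.44 = 26% and 0.6 × 0.76 = 46%. The trend comes from judgement alone. This shows the mechanism; it does not predict the result.

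**Step 5. The Schedule against the AE window.** Section 8.3.4 runs the window from allocation to 30 days after drug stop. The Schedule's AE row starts at infusion, and its last marks are the end-of-treatment and 72-hour visits; the mid-term and long-term columns are blank. No scheduled check falls at the end of the window.

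**The case against.** Several points on the other side are sound.

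- **The related category is wide.** Under 8.3.3.2 timing alone can make an event related, and the product is always to be under suspicion. Many AEs during the infusion may therefore be entered. What remains exposed is mainly non-serious AEs given another cause, or arising in the weeks after the infusion.
- **Other safety data do not pass through the filter.** Heart rate and blood pressure are eCRF items in their own right, and the major neonatal morbidities are recorded separately.
- **The omitted AEs are not lost.** They stay in the notes and could be retrieved, although no section plans to do so.
- **The stakes are bounded.** This is a secondary endpoint in at most 30 infants, and the primary endpoint is untouched.

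Three stronger readings are tempting and should be resisted.

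- A reader might infer that AE rates will certainly be undercounted, and by a large fraction. Section 6.2, the Schedule legend and the wide related category all leave room for near-complete capture, and nothing in the protocol anchors a percentage.
- A reader might infer from the Schedule that AEs go uncollected for most of the window. The Schedule does mark a check at end of treatment, which section 8.1.1.7 places when the infusion has stopped. The 72-hour visit is timed from birth, not from allocation. Section 8.3.4 requires collection for the full period whether or not a visit is scheduled. A missing check is an operational weakness, not proof of missing data.
- A reader might infer from the word *severe* in the endpoint that the wrong events will be analysed. Section 8.2 says *serious* and 8.3.2 separates the two terms, so this is a slip of wording.

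None of this gives the all-AE frequency a defined data source. Selective capture is a legitimate choice, but then the endpoint has to say so.

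**Conclusion.** The inconsistency is real. The endpoint and analysis promise frequencies of all AEs by dose group, while the rule in 8.3.4 and 8.3.5 omits non-serious AEs judged unrelated, and section 6.2 and the Schedule conflict with that rule. If the restricted rule is followed and the eCRF is the analysis source, the reported AE rate may be too low, and its comparison between doses would depend on causality opinions formed with the dose known. The amount cannot be estimated from the documents. SAE counts are not affected. The point deserves correction before data collection because it changes what the safety comparison can claim, but it does not bear on the dose-finding result.

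**What to change.** Choose one of two routes.

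1. **Widen the capture.** In 8.3.4 and 8.3.5, enter every AE in the eCRF, whatever its causality, for the whole window already stated: allocation to 30 days after drug stop. Record causality as an attribute of the event, not as a condition of entry. Align section 6.2 with this, and add an AE check at 30 days after drug stop to the Schedule. A shorter period of full capture, ending soon after the infusion, would leave the same filter in place for most of the window and would not resolve the mismatch.
2. **Narrow the endpoint.** If capture stays restricted, restate the endpoint and analysis in 1.1, 3, 8.2 and 9.1.2 as adverse reactions plus all SAEs, and bring section 6.2 and the Schedule into line.

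Under either route, change *severe* to *serious* in the endpoint in 1.1 and 3.

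Route 1 costs modest extra data entry for at most 30 infants and one further check each. Route 2 is a change of wording, but the trial then claims less, and the comparison of non-serious events still rests on causality judged with the dose known.
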